#### Participant identification and recruitment

Participants will be identified from existing CAMHS referrals where young people have self-reported DSEs. Research staff will regularly attend multidisciplinary team meetings to support clinicians in identifying eligible participants. Clinicians will provide initial study information to families and seek verbal consent for contact by the research team. The research team will subsequently contact interested families to provide full study details and obtain informed consent from parents/caregivers and young people aged 16 years and over and assent from young people. aged 15 years and under, documented in accordance with local governance procedures.

#### Screening and enrolment

Following consent and assent, screening assessments using the MAVIC and MUSEQ measures will confirm eligibility prior to enrolment. Consenting participants will complete baseline assessments (T0) before randomisation. Young people and parents/caregivers will be offered choices regarding the format and location of assessments (in-person, telephone or video call) and whether to complete these independently or together.

#### Sampling and recruitment targets

As a feasibility trial, a formal power calculation is not required.^49 50^ In line with recommendations for pilot trials, we aim to randomise 60 young people and parent/caregiver dyads.^51 52^ This sample size is considered sufficient to estimate outcome measure variability and inform the design of a future definitive trial. Recruitment will take place over 19 months, with a minimum target of four participants per month in the first year. A recruitment review will be conducted at month 12, with contingency plans to extend to additional NHS trusts if 75% of the target sample has not been achieved 6 months before the end of the trial.

#### Consent, assent and withdrawal

Informed consent and assent will be obtained prior to participation in each stage of the study (T0, T1, T2). Participants may provide consent via signed hard copy, electronic form or audio-recorded verbal consent, depending on preference. The consent process will be clearly documented, and participants will be reminded that participation is voluntary and can be withdrawn at any time without affecting their access to usual clinical care. If a participant withdraws but then wishes to opt back in, they may do so if this is within four weeks of their six-month post-randomisation date for T2 data collection. Additional optional consent provisions will cover audio-recording assessments, use of anonymised data for secondary analysis, future research contact, teaching and sharing study results. Based on media interest in our work in this area previously, there is also an option for participants to opt-in to receive information about future media enquiries or invitations. In line with the Standard Protocol Items: Recommendations for Interventional Trials (SPIRIT statement^53^, predefined criteria for the discontinuation or interruption of the intervention will be applied at the individual participant level, with intervention delivery paused or possibly stopped where a SAE is assessed as being related to the ChUSE intervention procedures.

#### Remuneration and expenses

Participants will receive a £10 shopping voucher as a thank you for completing outcome assessments at T0, T1 and T2. Reasonable travel expenses can be reimbursed on request for in-person research appointments, although the majority of trial procedures will be conducted remotely or during routine clinic visits.

## Measures

### Eligibility screening and baseline assessments

Eligibility will be confirmed via a short screening form (age and presence of at least one self-identified current DSEs using the MAVIC and USQ). Those eligible will proceed to baseline (T0) assessments, including demographic, clinical history and validated outcome measures. Ineligible participants will be debriefed, receive a voucher and be offered a summary of their screening results to share with their clinical team.

Assessments will be flexible, delivered face-to-face or remotely, with options for breaks or multiple shorter sessions. After completing the baseline assessment, the young person (and, by proxy, their parent/caregiver) will be randomised to receive either TAU or ChUSE+TAU. Young people’s preferences around who is present during assessment will be respected. Measures will be repeated at T1 and T2, as shown in table 1 and table 2.

**Table 1 T1:** Assessments for children and young people

T0 (baseline)	T1 (3-month follow-up)	T2 (6-month follow-up)
Screen: MAVIC	MAVIC	MAVIC
Screen: Unusual Sensory Experiences Questionnaire	–	–
Demographics	–	–
Strengths and Difficulties Questionnaire (SDQ)	SDQ	SDQ
Kidcope Scale	Kidcope Scale	Kidcope Scale
The Stirling Children’s Wellbeing Scale	The Stirling Children’s Wellbeing Scale	The Stirling Children’s Wellbeing Scale
Self-Compassion Scale Short Form (SCS-SF)	SCS-SF	SCS-SF
EQ-5D-Y	EQ-5D-Y	EQ-5D-Y
CHU-9D	CHU-9D	CHU-9D
CSS	CSS	CSS
		TAU checklist

CHU-9D, Child Health Utility Instrument; CSS, Child Stigma Scale; EQ-5D-Y, EuroQol 5-Dimensional Questionnaire for Youth; MAVIC, Manchester Voices Inventory for Children; TAU, treatment as usual.

**Table 2 T2:** Parent/carergiver measures

T0 (baseline)	T1 (3-month follow-up)	T2 (6-month follow-up)
Demographics	–	–
SDQ (parent version)	SDQ (parent version)	SDQ (parent version)
Adult Wellbeing Scale	Adult Wellbeing Scale	Adult Wellbeing Scale
Parental Stress Scale	Parental Stress Scale	Parental Stress Scale
Coping Health Inventory for Parents	Coping Health Inventory for Parents	Coping Health Inventory for Parents
EQ-5D	EQ-5D	EQ-5D

EQ-5D, EuroQol-5 Dimension questionnaire; SDQ, Strengths and DifficultiesQuestionnaire.

Participants do not have to complete all questions in the outcome measures. At the end of the baseline assessment, participants will be informed of their trial arm allocation by a member of the research team.

### Randomisation and blinding

Participants will be randomly allocated on a 1:1 basis to either (1) ChUSE talking therapy plus parent sessions alongside TAU or (2) TAU alone. Randomisation will be conducted independently using a web-based service (sealedenvelope.com), with concealed allocation via a pseudo-random sequence employing random permuted blocks of varying sizes, unknown to the study team.

Following baseline assessment, research workers will notify the chief investigator (CI) or a delegate about participant eligibility for randomisation. The CI or trial therapist (or delegate) will then enter the participant ID into the secure online system, which will immediately generate the allocation. Allocation outcomes will be communicated only to unblinded team members (CI, Co-CI and the trial therapist) and centrally logged on the secure platform and a restricted-access randomisation log.

Blinding will be maintained for research workers and trainees responsible for data collection. Research workers and trainees will not access clinical notes or treatment information post-randomisation and will be routinely reminded, along with participants and clinical teams, to avoid disclosing treatment allocations during assessments. The CI, therapist and co-investigators will remain unblinded in line with standard practice for psychological intervention trials. Any breaches of blinding will be documented, and where possible, follow-up will be reassigned to a blinded researcher.

### Interventions

#### Comparator: treatment as usual

Participants allocated to the TAU arm will continue to receive care as usual in CAMHS. The trial team will not intervene in routine care or request clinicians to withhold any referrals or treatments typically offered to participants. This aligns with established practices for pragmatic psychological intervention trials.^54^ In the absence of national clinical guidelines specifically addressing DSEs for children, clinicians will be asked to describe what interventions and supports they provide to these young people and their families. These data will be systematically collected and tabulated using a structured checklist and free-text responses, offering novel insights into routine clinical practices for DSE.^55^

#### ChUSE intervention

The feasibility trial will deliver the ChUSE intervention through qualified, NHS-employed, HCPC-registered clinical psychologists trained and supervised in the protocol by the study’s CI. The manualised intervention will comprise ideally seven 50-min sessions (four child-focused and up to three parent coaching sessions) delivered over a 3-month period. While the intervention will always remain brief, there is some flexibility in the number of sessions offered to young people to support engagement for up to a maximum of six sessions. This is to allow for pacing of content and accommodate breaks or shorter sessions as required by families with different needs. There will also be a session zero offered to all participants in the trial arm to attend as a child–parent/caregiver dyad. After each session, the therapist will complete an adherence checklist to monitor progression towards therapy milestones, the use of intervention strategies in line with the manual and any deviations.^56^

Parents/caregivers of children in the intervention arm will be offered the parent sessions alongside the child-focused therapy. Importantly, parental engagement in the parent sessions will not be a prerequisite for children to access individual therapy. The structure and delivery format of both child and parent components were informed by PPIE consultations, which recommended offering a choice of in-person or online sessions via Microsoft Teams to enhance accessibility.

#### ChUSE child-focused intervention

The child-focused therapy is a psychological intervention targeting DSEs, delivered across 4–6 structured sessions. Content draws on contemporary research on child distress, USEs and psychosis-like phenomena.

The first session will focus on exploring the young person’s DSEs and goals, psychoeducation and normalisation.^1 30 57^The second will introduce formulation and multisensory coping strategies based on compassion-focused therapy principles, shaped by recommendations from young people with lived experience and the growing compassion for voices literature.^17 23 32^The third session will include cognitive appraisal work, coping skills practice and simple self-formulation exercises.^31 33^The final session will focus on compassion-focused reflection, consolidation of coping strategies and safety/future planning.

#### ChUSE parent training programme

Parents/caregivers will be invited to attend three structured sessions designed to complement the child’s therapy.

The first session offers psychoeducation, normalisation, reappraisal strategies and therapist-guided, scenario-based problem-solving.^19 57^The second introduces compassion-focused coping techniques and self-kind containment strategies.The third provides therapist-guided reflective discussions, consolidating new knowledge and coping skills.

Between-session homework will involve reading psychoeducational materials and practising coping strategies, facilitating skills generalisation and enhancing therapeutic outcomes.^58^

#### Fidelity and process monitoring

With participant consent, therapy sessions may be audio- or video-recorded for supervision and fidelity monitoring purposes. Declining to consent for recording will not affect the care received. Recordings will be destroyed following review or fidelity assessment.

Fidelity will be monitored via a therapist-completed intervention integrity checklist developed for the study. Additionally, a random sample of 10% of recorded sessions will be rated using the CBT-SCYP to assess adherence to the ChUSE manual.^59^ The therapeutic alliance will also be measured post-intervention using the Therapeutic Alliance Scale for Children and Caregivers, completed by children and parents/caregivers.^60^

### Follow-up assessments and safeguarding procedures

Participants will be invited to complete follow-up assessments at 3 months (T1) and 6 months (T2) post-randomisation. These assessments will replicate the baseline battery of measures, as shown in tables 1 and 3. To enhance active safety monitoring, AEs will be systematically assessed during each contact point and through consultation with clinical notes.

**Table 3 T3:** Measures and completion times

Instrument used in the proposed trial	Number of items	Indicative completion time
Strengths and Difficulties Questionnaire Self-Report version for 11–17-year-olds^69^	25	10–15 min
Manchester Voices Inventory for Children (MAVIC;^23^)	18	10–12 min
Unusual Experiences Questionnaire (MUSEQ;^70^)	9 (only issued at T0)	10–15 min
Stirling Children’s Wellbeing Scale^71^	12	8–10 min
Brief Self-compassion Scale^72^	12	8–10 min
KidCOPE scale^73^	15	10–20 min
EQ-5D-Y^63^	5	5 min
Child Health Utility Instrument (CHU-9D;^64^)	9	5–8 min
Child Stigma Scale (CSS) – adapted multisensory experiences^74^	7	5 min
Treatment as usual checklist (TAU checklist)	12	8–10 min

EQ-5D, EuroQol-5 Dimension questionnaire; EQ-5D-Y, EuroQol 5-Dimensional Questionnaire for Youth; UEQ, Unusual Experiences Questionnaire.

Each assessment is expected to last approximately 1 hour, with options for breaks or multiple shorter sessions to accommodate participants’ needs (see table 3). T2 may take up to 2 hours, as this data point includes qualitative interviews. For all participants, there is then an option to provide further qualitative feedback through a Qualtrics survey, based on the same questions as the semi-structured interview guides. There is one survey for CYP and one for parents/caregivers. On completion of the final follow-up, participants will be formally debriefed about the feasibility of the RCT and, where consent has been provided, reminded about possible future contact for research updates or follow-up studies.

To minimise missing data, the research team will make multiple attempts to contact participants before considering them lost to follow-up. Data collection methods will include in-person, telephone, video conferencing or postal options. Any spurious or incomplete data will be reviewed by the research team, who will determine appropriate actions such as verification or re-collection.

Safeguarding procedures will adhere to local and national guidelines. The CI will be informed of any safeguarding concerns and referrals will be made to the appropriate safeguarding team for the child’s local area. In cases of immediate risk, the emergency duty team will be contacted directly. Contact details for safeguarding services across Greater Manchester’s 10 boroughs will be held by designated trial staff, and procedures will follow the Greater Manchester Mental Health NHS Foundation Trust safeguarding policies.

### Progression criteria

Progression to a definitive trial will be determined using pre-specified feasibility criteria across five domains (see table 4). Recruitment feasibility will be assessed by the number of parent–child dyads consented and randomised per month, alongside referral sources and reasons for non-eligibility or non-participation. Feasibility will be demonstrated if an average of at least three dyads are recruited per month. Recruitment of two dyads per month will indicate conditional feasibility, requiring the identification of additional recruitment strategies, while recruitment averaging one participant per month (fewer than 20 participants overall) will indicate that progression is not feasible within the current design. However, these criteria will be applied with some flexibility where there are contextual factors to consider, such as the impact of school holidays and national holidays on families’ engagement with services.

**Table 4 T4:** Progression criteria

Domain	Green	Amber	Red
Recruitment	≥3 dyads/month	2 dyads/month	≤1 /month (<20 total)
Intervention completion	≥70% complete	50–70%	<50%
Trial retention	≥70% retained	30–70%	<30%
Parent programme uptake	>70% uptake	50–70%	<50%
Safety (SAEs)	<5% SAE	5–10%	>10% SAE

SAEs, serious adverse events.

Intervention feasibility will be evaluated through adherence and attendance. Progression will be supported if at least 70% of participants allocated to the intervention arm complete the full course of treatment, defined as engagement with all four CYP sessions. Completion rates of 50–70% will indicate conditional feasibility, contingent on identifying barriers and potential adaptations informed by qualitative interviews and adherence data. Completion rates below 50% will indicate that progression to a definitive trial is not feasible without substantial modification of the intervention or delivery model.

Trial retention will be assessed by the proportion of participants completing end-of-treatment and follow-up assessments. Retention of at least 70% of participants will demonstrate feasibility. Retention rates between 30% and 70% will indicate conditional feasibility, requiring the development of strategies to address attrition, informed by reasons for withdrawal, recorded at the point of withdrawal in a participant tracker and qualitative interview data. Retention below 30% will indicate non-feasibility of progression under the current trial design.

The feasibility of including the parent training programme in a future definitive trial will be determined by parental uptake and attendance. Inclusion of the parent sessions will be considered feasible if more than 70% of parents allocated to the intervention arm take up the offer. Uptake of 50–70% will indicate conditional feasibility, dependent on evidence of session attendance, potential added benefit and health economic data suggesting cost-effectiveness. Uptake below 50% will indicate that inclusion of the parent sessions is not feasible within the current design.

Safety and acceptability of trial procedures will be assessed through monitoring of SAEs. Feasibility will be demonstrated if fewer than 5% of participants experience SAEs related to trial procedures. SAE rates between 5% and 10% will indicate conditional feasibility, requiring the identification of additional risk-mitigation strategies informed by qualitative data. SAE rates exceeding 10% will indicate that progression to a definitive trial is not feasible. All SAEs will be reviewed by the TSC Chair and reported to the sponsor as appropriate.

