#### Objectives

The primary objective is to assess key feasibility outcomes and gather data to inform the design of a future multi-site randomised controlled trial (RCT). Specifically, the study will examine:

The feasibility of recruiting children and their parents or caregivers to the trial.The retention of participants throughout the trial period.Engagement with and adherence to the intervention and trial procedures.The safety of the intervention and trial procedures.Estimation of key parameters to support a sample size calculation for a future definitive efficacy trial.

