#### Primary feasibility outcomes

The main feasibility outcomes for this study are as follows:

Recruitment rates, measured as the number of family units recruited and randomised per month.Participant retention rates, expressed as the proportion of participants completing outcome assessments at each time point.Treatment engagement and adherence, assessed by the number of sessions attended by young people and parents or caregivers allocated to both the ChUSE intervention plus TAU arm and the TAU-only arm.Treatment fidelity, determined by the extent to which trial therapists deliver the ChUSE intervention according to the intervention protocol, as measured by fidelity checklists.Safety of the intervention, evaluated through the monitoring and recording of adverse events (AEs) and serious adverse events (SAEs), both related and unrelated to the intervention or trial procedures, using detailed AE reporting forms.Preliminary signals of efficacy and estimation of parameters required for a future sample size calculation, with outcome data collected at baseline (T0), 3 months (T1) and 6 months (T2).

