#### Analysis of key feasibility outcomes

Descriptive statistics will be employed to summarise key feasibility and acceptability outcomes, including trial recruitment, retention, therapy engagement and treatment fidelity. Participant flow through the trial will be reported in accordance with the Consolidated Standards of Reporting Trials (CONSORT) extension for feasibility and pilot trials,^49^ detailing the number of referrals received per month, recruitment sources, number of participants contacted and assessed for eligibility, numbers consented (with reasons for ineligibility or declining participation when available), randomisation to trial arms, adherence to allocated interventions and retention at the 3- and 6-month follow-up assessments.

All quantitative data analysis will be conducted according to a pre-specified statistical analysis plan prepared by our trial statistician (co-author [name]) and available on request from the corresponding author. Descriptive analyses of therapy session records and fidelity checklists will estimate the adherence of therapists to the intervention protocol. AEs and SAEs will be tabulated by trial arm and reviewed to assess the safety and acceptability of the intervention and study procedures.

In addition, descriptive statistics (mean, SD, minimum, maximum, range and percentage of missing data) will be reported for all outcome measures at baseline and follow-up assessments, disaggregated by trial arm. These data will inform feasibility parameters for a future definitive trial, including estimates of variance and preliminary outcome differences. No hypothesis testing for clinical effectiveness (p values) will be conducted, but where appropriate, mean differences, SD and 80% CIs will be calculated at follow-up time points to provide a preliminary indication of the ‘promise of efficacy’ of the ChUSE intervention on valued trial outcomes.^61^

To support the feasibility of future health economic evaluation, the completeness and quality of data collected using the EQ-5D,^62^ EQ-5D-Y^63^ and CHU-9D^64^ will be summarised. Intervention and TAU service costs will be estimated using national unit cost data from NHS England and the Personal Social Services Research Unit.

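### The safety progression criterion does not count the same SAEs in its green, amber and red bands, and its green band as worded leaves out SAEs related to the therapy

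*Protocol article*

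**What the plan says.** The Progression criteria section of the protocol article gives the safety criterion twice.

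- **Text, green:** "Feasibility will be demonstrated if fewer than 5% of participants experience SAEs related to trial procedures".
- **Text, amber:** "SAE rates between 5% and 10% will indicate conditional feasibility".
- **Text, red:** "SAE rates exceeding 10% will indicate that progression to a definitive trial is not feasible".
- **Table 4:** the safety row gives the same cut-offs (below 5%, 5 to 10%, above 10%) and names SAEs only, with no mention of relatedness.

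Elsewhere the article treats the therapy and the trial procedures as two things. The Objectives list "The safety of the intervention and trial procedures". Primary feasibility outcomes include safety of the intervention, assessed from events "both related and unrelated to the intervention or trial procedures". Under Analysis of key feasibility outcomes, "AEs and SAEs will be tabulated by trial arm and reviewed to assess the safety and acceptability of the intervention and study procedures". For individual discontinuation, the section on consent, assent and withdrawal uses a third term: delivery is paused or "possibly stopped where a SAE is assessed as being related to the ChUSE intervention procedures".

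**The concern.** The percentages agree between text and table, but what is counted does not. Relatedness is required in the green sentence and nowhere else in the criterion, and that sentence names trial procedures alone. Two consequences follow from a literal reading.

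- Green can be met however many SAEs are attributed to the therapy, which is the harm most relevant to the decision on a definitive trial.
- Red can be met by events unrelated to therapy or trial, including events in the TAU arm, so progression could be blocked with no therapy effect at all.

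The criteria are presented as pre-specified. If the definition has to be chosen once the SAEs are known, that purpose is lost.

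**Working it through.** There is no power or sample-size figure to reproduce. The check sets the bands side by side and converts them to counts.

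**Inputs.** 60 dyads (Sampling and recruitment targets); 1:1 allocation (Randomisation and blinding), so about 30 children per arm; cut-offs of 5% and 10% (Progression criteria). The article gives no background SAE rate, so the rates in step 4 are assumptions.

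**1. Cut-offs as counts of children**

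- Over 60: 5% is 3 and 10% is 6. Green is 0–2, amber 3–6, red 7 or more.
- Over 30: 5% is 1.5 and 10% is 3. Green is 0–1, amber 2–3, red 4 or more.

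**2. Unrelated events only.** Seven of 60 children have an unrelated SAE and none has a related one.

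- Green sentence: 0/60 = 0%, so green.
- Red sentence, and Table 4 as printed: 7/60 = 11.7%, so red.

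**3. Therapy-related events only.** Four ChUSE children have a therapy-related SAE and nobody has one from trial procedures.

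- Green sentence: 0%, so green.
- Unqualified SAE rate over all randomised children: 4/60 = 6.7%, so amber.
- Over children allocated to ChUSE: 4/30 = 13.3%, so red.

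The denominator matters here. For intervention completion and parent uptake the same section specifies the intervention arm; for safety it says only participants.

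**4. How easily the unqualified reading gives red.** With X ~ Binomial(60, p) and the same any-cause SAE risk p in both arms (no therapy effect),

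P(red) = P(X ≥ 7) = 1 − Σ(k=0 to 6) C(60,k) p^k (1−p)^(60−k), and P(green) = P(X ≤ 2).

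| Assumed any-cause risk p | P(green) | P(red) |
|---|---|---|
| 5% | 0.417 | 0.030 |
| 10% | 0.053 | 0.394 |
| 15% | 0.004 | 0.815 |

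For contrast, if only related SAEs count and their risk is assumed to be 1% or 2%, P(green) over 60 is 0.978 or 0.881 and P(red) is close to zero. The choice of numerator can therefore settle the colour.

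**The case against.** **The table is shorthand.** Other rows of Table 4 are abbreviated too: the completion row omits both the arm and the four-session definition, which the text supplies. The safety row may be meant to inherit the text's limit, and the table never says that SAEs of any cause count. That is fair, and a deliberate any-cause rule in the table cannot be inferred. It does not resolve the matter, because the text drops the limit in its own amber and red sentences and so offers no single definition to inherit.

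**Amber and red may refer back to green.** This is possible, and it would give one numerator. It would then be SAEs related to trial procedures in all three bands, and therapy-related SAEs would be outside the whole criterion.

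**Trial procedures may loosely include the therapy.** The discontinuation wording speaks of intervention procedures, which lends this some support. But the Objectives, the primary outcomes and the analysis section each name the intervention separately, and nothing says that the term covers it.

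**Harm is monitored anyway.** This stands. Related and unrelated events are recorded, SAEs are tabulated by arm, relatedness is assessed, and the TSC Chair reviews all SAEs. A reader might infer that the plan cannot detect harm from the therapy; the article does not support that. Only the green band as worded omits it.

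**The denominator is a matter for the analysis plan.** Leaving out the analysis set would not be a fault on its own. It matters here because the article fixes percentage thresholds that give different colours over 30 and 60. A reader might also infer a denominator of 120 by counting parents. The article points against this: Trial design equates all participants with 60 dyads, and the parent is randomised by proxy with the child.

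**Conclusion.** The inconsistency is on the page and does not depend on any assumed rate. The green sentence carries a relatedness limit that the amber and red sentences and Table 4 lack, and the limit names only trial procedures. One set of data can meet green and red together (7 of 60 with unrelated SAEs only). Four therapy-related SAEs can be green, amber or red according to the sentence and denominator used.

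It would go too far to say that the text confines all three bands to procedure-related SAEs, since only green is so confined. The probabilities of red (about 3%, 39% and 82%) rest on assumed any-cause risks of 5%, 10% and 15%, with independent events and equal risk in both arms. They illustrate sensitivity and do not predict this trial's result. The defect is confined to the progression rule, but that rule decides whether a definitive trial goes ahead, so it should be corrected before it is applied.

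**What to change.** Reconcile Table 4 and the safety paragraph of Progression criteria.

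1. Use one numerator for green, amber and red: children with at least one SAE assessed as related to the ChUSE intervention or to trial procedures.
2. State the denominator. If intervention-related SAEs are judged over children allocated to ChUSE and procedure-related SAEs over all randomised children, state that the worse of the two colours applies. A child whose SAE is related to both counts in both.
3. Report any-cause SAEs by arm alongside the traffic light.

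The sponsor keeps or resets the percentages; none is proposed here. An all-SAE criterion would also be internally consistent if applied to every band, but it would carry the sensitivity to background events shown above.

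The cost is wording only. The article already provides for relatedness to be assessed (section on trial endpoints, ethical and regulatory considerations and data management), so no new data are needed. The downside is coarseness: over about 30 children the rate moves in steps of 1/30 = 3.3%, so a second affected child leaves green and a fourth reaches red at the present cut-offs.
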